### Other measures

These are arrhythmia; blood pressure variability; biomarkers for atherosclerosis, such as hs-CRP, homocysteine, and total bilirubin; and blood lipids, such as triglycerides, total cholesterol, high-density lipoprotein, low-density lipoprotein, and nonesterified fatty acids [19].

### Interventions

The patients will be allocated to either the experimental or control group based on a blocked randomization sequence generated by SPSS 23.0 software for Windows.

### Surgical treatment

All patients will be treated with a CEA standard operation. After general anesthesia, the patient will be placed in the supine position, with the shoulder pad, head and neck facing the contralateral hyperextension position, and the basal blood pressure level will be maintained. During the operation, the changes in intracranial blood flow will be monitored by transcranial Doppler. The carotid artery and its branches will be dissected along the incision at the front edge of the sternocleidomastoid muscle. If the patient’s carotid artery bifurcation is high or the lesion area is extended, the digastric power can be cut off to block the distal end of the internal carotid artery. After dissecting the bifurcation of the common carotid artery, internal carotid artery, external carotid artery, and superior thyroid artery clearly, a blocking band will be sleeved, and appropriate blocking forceps will be selected for later use. After the preparation is finished, whole body heparin will be given at 1 mg/kg, and 1% lidocaine will be used for carotid sinus infiltration anesthesia. To avoid excessive blood pressure fluctuation, a longitudinal incision will be made to cut the blood vessel, peel off the plaque, and remove it as altogether as possible. Heparin saline will be used to wash the peeling surface, and the intimal flap will be floated to fix it. The blood vessel will be sutured, the blocking forceps will be loosened, and the blood pressure will be lowered by 10–20% of the basal blood pressure to reduce the risk of postoperative overperfusion. The subcutaneous tissue and skin will be sutured in turn. After suturing, the coagulation function will be checked urgently, and whether to use protamine to neutralize heparin will be decided according to the results.

In the experimental group, after suturing the blood vessels, the carotid sinus nerve will be searched for along the front of the internal carotid artery, separated and exposed approximately 1 cm in length to be entirely transected, and then the subcutaneous and skin will be sutured layer by layer.

### Postoperative treatment

Statins (double dose) will be used to strengthen lipid regulation and stabilize the plaque. Aspirin (100-mg QD) combined with clopidogrel (75-mg QD) will be utilized for antiplatelet therapy for 1 month, and then statins (conventional dose) and aspirin (100-mg QD) will be used for antiplatelet therapy for a long time.

### Baseline data collection

We will request consent for review of participants’ medical records and for the collection of blood samples to assess blood lipids, hs-CRP, homocysteine, liver function, and kidney function within 1 week before the operation [20]. The blood samples after inspection will be stored in special liquid nitrogen tanks for future use in auxiliary research. On the second day after the procedure, high-resolution-enhanced magnetic resonance imaging (MRI) will be reexamined to understand the recovery of the carotid canal cavity and plaque clearance for subsequent comparison. Carotid artery color Doppler ultrasound will be performed 1 week after the operation to understand plaque.

### Follow-up

Follow-up in the outpatient department will be performed every 3 months. At the same time, blood lipids, hs-CRP, homocysteine, liver function, and kidney function will be reexamined after obtaining informed consent. Carotid artery color Doppler ultrasound and carotid artery high-resolution enhanced MRI will be reviewed at 3 months, 6 months, 1 year, 2 years, and 2 years after the operation.

### Sample size

The determination of sample size was calculated by SPSS 23.0 software. Based on a previous study and clinical assumptions, carotid restenosis was 5–22% [4–6]. Our previous research showed that the restenosis rate of the carotid artery after CEA in our hospital was approximately 15%. The statistical parameters were set as follows: one-sided log-rank testing with 80% power, the probability of obtaining a false-positive with a statistical test at 0.05, and a 3-year follow-up time. Considering a potential dropout rate of 5% across both groups, it is estimated that 276 patients will need to be enrolled (138 participants per group).

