### Comparison of baseline data

*T*-tests will be performed for quantitative data that are usually distributed, and a nonparametric test will be used for quantitative data that are not normally distributed, including blood lipids, hs-CRP, homocysteine, liver function, and kidney function. The chi-squared (*χ*^2^) test will be used for counting data, including recovery of the carotid canal cavity and plaque clearance. A two-sided *P*-value < 0.05 will be considered statistically significant.

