### Comparison of therapeutic efficacy

The rate of carotid artery restenosis, plaque incidence, and stability of carotid arterial plaque will be analyzed by the chi-square (*χ*^2^) test between the two arms.

The size and thickness of carotid arterial plaque, carotid artery blood flow velocity, blood lipids, hs-CRP, homocysteine, and total bilirubin will be analyzed by *t*-test analysis.

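### The 80% power and N = 276 rest on a one-sided log-rank test with no stated effect size, while restenosis is to be analysed by chi-square and the only threshold in the analysis text is two-sided 0.05

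*Protocol article*

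**What the plan says.** All references are to the protocol article.

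- **Sample size** sets "one-sided log-rank testing with 80% power, the probability of obtaining a false-positive with a statistical test at 0.05" and "a 3-year follow-up time". With a 5% dropout allowance this gives 276 patients, 138 per group.
- On the effect, the same section opens with "Based on a previous study and clinical assumptions", cites a literature range of 5% to 22%, and adds "Our previous research showed that the restenosis rate of the carotid artery after CEA in our hospital was approximately 15" (per cent). It gives no experimental-arm rate, hazard ratio, difference or event count.
- **Outcomes** defines restenosis as stenosis of at least 50% on ultrasound and the restenosis rate as a proportion of patients. The Discussion makes this rate the main index.
- **Comparison of therapeutic efficacy** states: "The rate of carotid artery restenosis, plaque incidence, and stability of carotid arterial plaque will be analyzed by the chi-square" test. It gives no significance level or sidedness.
- **Comparison of baseline data** contains the only threshold in the analysis text: "A two-sided *P*-value < 0.05 will be considered statistically significant".
- None of the analysis sections, from Statistical analysis to Safety evaluation, mentions a log-rank, Kaplan-Meier or other time-to-event analysis.

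**The concern.** The document fixes two different tests for its main index. It also attaches its power to a one-sided error rate that the analysis text never repeats. A chi-square on a two-by-two table does not look at direction, so its usual 0.05 reading is two-sided. A result with a one-sided p of 0.04 in favour of neurectomy would succeed under the sample size rule and fail under the ordinary chi-square. The reader cannot tell which rule decides the trial.

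Separately, a sample size without its target effect cannot be checked. The reader cannot see what reduction in restenosis the trial is built to detect.

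**Working it through.** **Inputs from the document:** 138 per arm, 5% dropout, one-sided 0.05, 80% power, local restenosis rate about 15%.

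**Assumptions:** the 15% is the 3-year control rate (the text does not label it so); exponential event times; 138 × 0.95 ≈ 131 evaluable per arm.

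**1. Reproducing 276.** This cannot be done forwards, because no effect is stated. N depends strongly on it. Schoenfeld's formula, one-sided 0.05 with 5% dropout, gives these totals:

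| Assumed experimental rate | Total N |
|---|---|
| 5% | 200 |
| 6% | 272 |
| 7.5% | 431 |
| 10% | 1112 |

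**2. Back-solving the rate that 276 implies.** Let HR = ln(1 − p2)/ln(0.85) and expected events D = 262 × (0.15 + p2)/2.

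- Schoenfeld, power = Φ(√(D/4)·|ln HR| − 1.645). At p2 = 0.0612: HR = 0.389, D = 27.7, so Φ(2.486 − 1.645) = Φ(0.841) = 0.80.
- Freedman, power = Φ(√D·(1 − HR)/(1 + HR) − 1.645). At p2 = 0.0556: HR = 0.352, D = 26.9, so Φ(2.488 − 1.645) = Φ(0.843) = 0.80.

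The implied experimental rate is 5.6% to 6.1%, a relative reduction of 63% to 59%. Neither figure appears in the document.

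**3. Chi-square power at those rates, 131 per arm.** Power = Φ((d − z·s0)/s1), where d is the difference, s0 the pooled standard error and s1 the unpooled one.

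- p2 = 0.0556: d = 0.0944, s0 = 0.03752, s1 = 0.03707. With z = 1.645: Φ(0.881) = 81%. With z = 1.960: Φ(0.562) = 71%.
- p2 = 0.0612: d = 0.0888, s0 = 0.03797, s1 = 0.03757. With z = 1.645: Φ(0.701) = 76%. With z = 1.960: Φ(0.383) = 65%.

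Exact binomial enumeration of the uncorrected chi-square gives slightly more: 78% to 83% one-sided and 66% to 73% two-sided. Taking both methods together, the ranges are 76% to 83% one-sided and 65% to 73% two-sided.

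**4. Other assumed effects, two-sided 0.05, 131 per arm.** 15% versus 5%: 77% (normal) or 79% (exact). 15% versus 7.5%: 48% (normal) or 49% (exact).

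**5. Separating the test from its sidedness.** Simulation at 15% versus 6% (4000 runs, 138 per arm, 5% loss, visits at 3 and 6 months and 1, 2 and 3 years; losses before an event counted as event-free in the chi-square):

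| | Log-rank | Chi-square |
|---|---|---|
| One-sided 0.05 | 78.5% | 79.2% |
| Two-sided 0.05 | 67.9% | 68.1% |

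Changing the test moves power by less than 1 point. Changing the sidedness moves it by about 11.

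**The case against.** A reader might infer three stronger things, and the documents support none of them.

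- **That replacing log-rank by chi-square loses the power.** It does not: at equal sidedness the two agree within a point. Nor is the chi-square the reason 276 cannot be reproduced. The missing effect size is, and naming the log-rank test as primary would not supply it.
- **That the planned test simply has about 70% power.** This needs both a back-solved rate and a two-sided reading. The two-sided sentence stands under baseline comparison, and the efficacy section gives no sidedness. Read one-sided, the chi-square has 76% to 83% and there is essentially no shortfall. There is also a rival origin for the number. The unpooled two-proportion formula for 15% versus 5%, two-sided 0.05, gives (1.960 + 0.842)² × (0.15 × 0.85 + 0.05 × 0.95)/0.10² ≈ 137.4, or 138 per arm before dropout. If that was the calculation, the planned test is close to its stated power, and the faults are the log-rank label and the absent dropout allowance. This origin is equally undocumented.
- **That patients who leave early must be dropped or counted as free of restenosis.** The Randomization and blinding section refers to a statistical plan that is not shown. It may settle this, so it is no finding here.

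It is also fair to say that a comparison of proportions suits the endpoint as defined, with ultrasound at five fixed visits in Table 1. The log-rank test is not the only right answer.

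What stands is the mismatch in test, the unresolved sidedness and the missing effect size. These are stated or omitted in this document's own sample size and efficacy text, and an unseen analysis plan would not remove the conflict.

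**Conclusion.** The concern holds as an inconsistency plus a missing input, not as a proven arithmetic error. The stated 80% power belongs to a test and an error rate that the analysis text does not use, and 276 cannot be checked because its target effect is not given.

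The size is conditional. If the chi-square is read two-sided at 0.05, its usual form, power is about 65% to 73% at the rates that 276 implies for a one-sided log-rank test. It is about 77% to 79% if 15% versus 5% was meant, and about 48% if restenosis is halved to 7.5%. All of these assume 15% in controls over 3 years and 131 evaluable per arm. The first range also rests on an experimental rate inferred from N. The contradiction between the sections needs none of these assumptions.

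**What to change.** Name one primary test and one error rate, and use them in both sections. Either route is sound:

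1. In Comparison of therapeutic efficacy, make the log-rank test the primary intention-to-treat analysis, report Kaplan-Meier 3-year restenosis rates, and keep the chi-square as supportive.
2. Or rewrite Sample size for a comparison of proportions, so that it matches the chi-square.

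In both cases, state two-sided 0.05 for efficacy explicitly. In Sample size, give the sponsor's own assumed experimental-arm rate (not one reconstructed from 276), say that the 15% is the 3-year control rate if that is so, and restate the power that 276 patients, about 131 evaluable per arm, give under the chosen test.

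The cost is protocol wording and probably a less favourable stated power. No extra patients are needed, and the ultrasound visits that either analysis uses are already scheduled. The change should be made before any unblinded comparison.

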### Data collection and management

A case report form (CRF) will be completed by each participant before the intervention. The collection of baseline data, along with primary and secondary outcomes, will be recorded entirely in the CRF. Each participant (corresponding to a CRF) will be assigned a specific number by which the intervention and follow-up will be performed. Using ResMan, an Internet-based electronic data capture (EDC) tool, all information will be kept independently as double copies in a computer. The data files will be locked after a blind audit and when they are confirmed reliable. The CRF shall be owned by the principal investigator and shall not be provided to any third party in any form without the written approval of the principal investigator, who will oversee all of the final trial data. A follow-up registration form will be given to all patients to encourage retention. A researcher will collect the reason for the loss, survival condition, and recent outcome as an assessment for participants who stop the intervention. The original paper files will be kept in the filing cabinet of the sponsoring organization, and clinical data will be held for 5 years.

### Quality control

#### Composition of the coordinating center and trial steering committee

The trial will be performed by the neurosurgery of the Second Affiliated Hospital of Chongqing Medical University. There is no other coordinating center. The trial steering committee consists of the ethics committee of the Second Affiliated Hospital of Chongqing Medical University (ID: LKSD-2023-88) and the clinical research team. The research team consists of three principal investigators who oversee the study and are responsible for medical responsibilities, a study coordinator who plans patient visits, and an investigator who is responsible for data management and trial management. The research team meets monthly to assess the progress, identify potential test subjects, and work out logistical issues. A statistician was involved in the design of the trial and will be consulted on statistical issues throughout the study. [name], [name], and [name] will identify the enrolled patients in the outpatient department. A researcher will collect general patient information. To improve the reliability of the test and reduce the differences between operators, the following measures will be taken: all the operations will be led by [name], and all the operations will be photographed and recorded by video. The test data will be evaluated and counted by one person.

A data monitoring committee (DMC), consisting of neurosurgery experts and statisticians, will be established, independent of the sponsor and trial investigator. The DMC will assess the progress of the clinical trials, safety data, and essential efficacy data yearly. The DMC will assess the progress of the clinical trials, safety data, and essential efficacy data yearly. The REC meeting will also assess the ethics of the trial every year.

In the study, an inspector will verify the accuracy and completeness of the CRFs and compare them with the source documents yearly. During inspections, it must be ensured that the subject’s dose changes, treatment changes, adverse events, combined medications, missed visits, and examination omissions are noted in the CRFs. Additionally, they must confirm that the withdrawals and missed visits of the selected subjects have been recorded and explained in the CRFs. The inspector will also notify the researcher of errors, omissions, or unclear hand-writing in CRFs and ensure that the researcher or authorized person carries out a correction, addition, or deletion. The modification must be documented in writing, if necessary. The inspector will promptly inform the principal after each supervision and inspection. The experimental results will be published in relevant publications for public access.

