### Reports of adverse events

Adverse events (AEs) will be assessed primarily by electrocardiogram and blood pressure monitoring. The occurrence, severity level, management strategies, causality related to the experimental surgery, and termination of all adverse events (AEs) will be recorded and preserved during the clinical trials and follow-up. All severe adverse events (serve arrhythmia) will be reported promptly to the principal investigator and the research ethics committee (REC). The researchers and clinical trial institutions will ensure that the subjects are treated appropriately and informed truthfully of the relevant information. According to China’s Management Specification for Classification and Sort of Surgical and Invasive Procedures in Medical Institutions, researchers are responsible for the cost of dealing with adverse reactions and compensation for patients who suffer adverse reactions. Participants are not provided with specific posttrial care (Table 1).

**Table 1 Tab1:** The flow diagram of enrollment, allocation, interventions, and follow-up for participants

	Enrollment	Allocation	Intervention		Follow-up				
			CEA	neurectomy	3 M	6 M	1 Y	2 Y	3 Y
Timepoint	1 week	0	1 week		3 years				
Enrollment									
Eligible screen	×								
Informed consent	×								
Demographic & medical data	×								
Random allocation		×							
Interventions									
Experimental group			×	×					
Control group			×						
Assessments									
Color Doppler ultrasound	×				×	×	×	×	×
HRMR	×				×	×	√	√	×
ECG	×				×	×	×	×	×
Biomarkers for atherosclerosis	×				×	×	×	×	×
Adverse events					×	×	×	×	×

*CEA* carotid endarterectomy, *HRMR* high-resolution enhanced nuclear magnetic resonance, *ECG* electrocardiogram, *M* month, *Y* years

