### Trial status

The trial started on July 18, 2023, and recruited 13 patients in our hospital. The trial was started according to the protocol in its second version dated March 23, 2023. There were minor protocol modifications after starting the trial (versions 3.0, date July 30, 2023); the only change was that the total sample size was revised to 276 patients, and this change had no impact on the study conduct. According to the planned timeframe, recruitment will be ongoing until March 31, 2024, and patient follow-up is expected to be completed by March 31, 2027. Upon completion, the results of the trial will be shared in an open-access journal. The protocol modifications will be submitted to the REC and the Chinese Clinical Trial Registration authority for review and record by website uploading.

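### The ethics committee is listed as part of the steering committee, and severe event reports are routed to it and the principal investigator, while the independent DMC is stated to assess safety data only yearly

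*Protocol article*

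**What the plan says.** All references are to the protocol article.

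- **Composition of the coordinating center and trial steering committee.** "The trial steering committee consists of the ethics committee" of the hospital and of the clinical research team. On that team: "The research team consists of three principal investigators who oversee the study". A DMC independent of sponsor and investigator is to look at progress, safety and efficacy data once a year. Separately: "The REC meeting will also assess the ethics of the trial every year".
- **Reports of adverse events.** Severe adverse events "will be reported promptly to the principal investigator and the research ethics committee". No other recipient is named.
- **Interim analysis.** One safety check is planned, once half the patients have been enrolled and have completed 3 years of follow-up. The only condition given for ending the trial is a significantly higher restenosis rate in the experimental arm.
- **Trial status.** The trial started on 18 July 2023, and "recruitment will be ongoing until March 31, 2024". Follow-up is to end on 31 March 2027. Protocol modifications go to the REC and to the registry.
- **Recruitment and eligibility criteria.** Enrolment is to take up to 3 years.

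**The concern.** Two statements about oversight fit together badly.

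First, the ethics committee is listed as a component of the steering committee, alongside the investigators whose trial it reviews. A body that helps to steer a trial is not well placed to review it from outside. If the sentence is only loose drafting, it still describes the governance wrongly.

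Second, both named recipients of severe event reports then belong to that same committee. The DMC, which has the stated independence, has no stated route to individual reports and a stated rhythm of one look a year.

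This matters because the experimental step is a complete nerve transection done once, during the operation, and cannot be withdrawn from a treated patient. Independent review of a cluster of severe events can protect only those not yet operated on, so the timing of that review against recruitment decides how useful it is. The point concerns who receives the reports and when. It does not concern which events are reportable.

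**Working it through.** **1. Reproducing the plan's own date.** Recruitment end 31 March 2024 + 3 years of follow-up = 31 March 2027. This matches Trial status.

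**2. Recruitment window on the Trial status dates.** 18 July 2023 to 31 March 2024 = 257 days; 257 / 30.4375 = 8.4 months. This is shorter than one yearly interval.

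**3. First yearly DMC review.** No DMC date or starting point is given. Assumption: yearly counts from trial start.
- Start + 12 months = 18 July 2024.
- 31 March to 18 July 2024 = 109 days after recruitment closes.
- If the last operation follows the last enrolment by up to 2 weeks (also an assumption), it falls by 14 April 2024, and the gap is 109 − 14 = 95 days.

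On these assumptions all 276 patients, 138 of them experimental, would have been operated on before the first review. The implied pace is 276 / 8.4 = about 33 patients a month.

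**4. The same question on the 3-year enrolment.** With even accrual, 276 / 3 = 92 patients a year, 46 of them experimental. Reviews at 12 and 24 months would find about 92 and 184 of 276 enrolled. The DMC would then look during recruitment, with about 92 patients enrolled between one review and the next.

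**5. Whether the planned safety check fills the gap.** It needs 3 years of follow-up in half the patients.
- Trial status dates, even accrual: half enrolled at about 23 November 2023; + 3 years = about 23 November 2026, or 967 days after recruitment closes.
- 3-year enrolment: half enrolled at 1.5 years; 1.5 + 3 = 4.5 years after the start, against an enrolment end at 3 years.

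On either timeline the check comes after recruitment has closed, and its stated trigger is restenosis, not adverse events.

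**6. Other routes in the text.** The inspector described under Quality control verifies case report forms yearly and informs the principal. Under Data collection and management, case report forms may not go to a third party without the principal investigator's written approval. Neither gives the DMC an earlier view.

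| Body | Stated independent of sponsor and investigator | Named recipient of severe event reports | Stated review of the trial |
|---|---|---|---|
| Principal investigator | No | Yes, promptly | Monthly team meeting |
| REC / ethics committee | No; listed on the steering committee | Yes, promptly | Yearly |
| DMC | Yes | No | Yearly, plus the one interim check |

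**The case against.** The strongest reply is that prompt reports to the investigator and the ethics committee, with periodic DMC review of accumulated safety data, is a coherent division of labour. Whether the DMC also receives expedited reports, when it first meets and whether it can be convened early are often left to a charter or the full protocol, and this is a condensed article. That has force: silence about the DMC under Reports of adverse events does not show that the DMC is excluded. What remains is that the article does name the recipients and does state the DMC's rhythm, and nothing in it adds an earlier view.

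A reader might infer that the DMC will first look only after every operation is done. The documents do not support that as a flat statement. No DMC date is given, the yearly cycle has no stated starting point, and an earlier first meeting is possible. The result also needs the short recruitment period, which conflicts with the 3-year enrolment. The pace of about 33 a month is only implied by the dates, in one hospital with one lead operator; Trial status reports 13 patients recruited when it was written.

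A reader might also infer that no independent body sees a severe event before the yearly review. That is too strong. The REC is told promptly. Doubt about its independence rests on a single sentence about committee membership, which gives the steering committee no stated role in safety. It also rests on reading the REC as that same ethics committee. That is the natural reading, as no other is named, but the text does not spell it out.

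**Conclusion.** The point stands in a limited form, as a cheap improvement. The ethics committee's place on the steering committee, and a severe event route that names the principal investigator and the REC but not the DMC, are on the page and do not depend on any dates. Taking the REC to be the hospital ethics committee is an inference.

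The size of the timing problem is conditional. It ranges from a first DMC review 109 days after recruitment closes (257-day recruitment, yearly cycle counted from trial start) to reviews within recruitment about 92 patients apart, 46 of them experimental (3-year enrolment, even accrual). The interim safety check does not narrow either case. The documents do not establish that independent review is impossible while patients are still being operated on; they simply do not secure it.

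**What to change.** 1. Under Reports of adverse events, state that each severe adverse event report goes to the existing DMC at the same time as to the principal investigator and the REC.
2. Under Composition of the coordinating center and trial steering committee, state that the ethics committee is separate from the steering committee and keeps its approval and yearly review role.
3. Reconcile the recruitment periods in Recruitment and eligibility criteria and in Trial status. If the short period stands, set the first DMC safety review before recruitment closes.

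The cost is a few sentences of protocol text, slightly more reading for the DMC and possibly one earlier meeting. No extra patients or study procedures are needed.
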